## Abstract

**Background:**

Paediatric acute respiratory distress syndrome (PARDS) is a manifestation of severe, life-threatening lung injury necessitating mechanical ventilation with mortality rates ranging up to 40–50%. Neuromuscular blockade agents (NMBAs) may be considered to prevent patient self-inflicted lung injury in PARDS patients, but two trials in adults with severe ARDS yielded conflicting results. To date, randomised controlled trials (RCT) examining the effectiveness and efficacy of NMBAs for PARDS are lacking. We hypothesise that using NMBAs for 48 h in paediatric patients younger than 5 years of age with early moderate-to-severe PARDS will lead to at least a 20% reduction in cumulative respiratory morbidity score 12 months after discharge from the paediatric intensive care unit (PICU).

**Methods:**

This is a phase IV, multicentre, randomised, double-blind, placebo-controlled trial performed in level-3 PICUs in the Netherlands. Eligible for inclusion are children younger than 5 years of age requiring invasive mechanical ventilation with positive end-expiratory pressure (PEEP) ≥ 5 cm H_2_O for moderate-to-severe PARDS occurring within the first 96 h of PICU admission. Patients are randomised to continuous infusion of rocuronium bromide or placebo for 48 h. The primary endpoint is the cumulative respiratory morbidity score 12 months after PICU discharge, adjusted for confounding by age, gestational age, family history of asthma and/or allergy, season in which questionnaire was filled out, day-care and parental smoking. Secondary outcomes include respiratory mechanics, oxygenation and ventilation metrics, pulmonary and systemic inflammation markers, prevalence of critical illness polyneuropathy and myopathy and metrics for patient outcome including ventilator free days at day 28, length of PICU and hospital stay, and mortality

**Discussion:**

This is the first paediatric trial evaluating the effects of muscular paralysis in moderate-to-severe PARDS. The proposed study addresses a huge research gap identified by the Paediatric Acute Lung Injury Consensus Collaborative by evaluating practical needs regarding the treatment of PARDS. Paediatric critical care practitioners are inclined to use interventions such as NMBAs in the most critically ill. This liberal use must be weighed against potential side effects. The proposed study will provide much needed scientific support in the decision-making to start NMBAs in moderate-to-severe PARDS.

**Trial registration:**

ClinicalTrials.govNCT02902055. Registered on September 15, 2016.

## Background and rationale {6a}

Paediatric acute respiratory distress syndrome (PARDS) is a manifestation of severe, life-threatening lung injury. The prevalence of PARDS in critically ill, mechanically ventilated children may be as high as 10% of all children admitted to the paediatric intensive care unit (PICU) with mortality rates ranging up to 40–50% [1]. The disease is characterised by massive pulmonary inflammation, alterations in surfactant homeostasis and ventilation/perfusion mismatching leading to severe hypoxemia and multiple organ dysfunction [2]. Mechanical ventilation (MV) has added significantly to the survival of PARDS patients but also induces a pulmonary inflammation (biotrauma) that aggravates pre-existing lung injury (double-hit), a concept known as ventilator-induced lung injury (VILI) [3–5].

Critical care practitioners have adopted the philosophy of maintaining spontaneous breathing in mechanically ventilated patients as much as possible. However, a study in adults with severe ARDS challenged these practices. Early use of neuromuscular blocking agents (NMBAs) in adults with severe ARDS, defined as PaO_2_/FiO_2_ ratio less than 150 mmHg, resulted in improved 90-day survival and increased time off the ventilator without increasing muscle weakness [6]. In this study, 340 patients with early severe ARDS, meeting criteria within 48 h of ICU admission, were randomised to cisatracurium besylate or placebo once adequately sedated. After adjustment for baseline PaO_2_/FiO_2_, plateau pressure and the Simplified Acute Physiology Score, the cisatracurium group had a hazard ratio for death at 90 days of 0.68, (95% confidence interval [CI], 0.48 to 0.98; *P* = 0.04), compared to the placebo group. These findings remained consistent when combined in a meta-analysis with earlier, smaller studies from the same group of investigators [7]. Additional beneficial effects of NMBAs observed included sustained improvement in oxygenation, less organ dysfunction, and a lower pro-inflammatory response [8–10]. However, the practice change that followed this trial came under scrutiny after the publication of the Re-evaluation Of Systemic Early Neuromuscular Blockade (ROSE) trial in 2019 [11]. This trial was designed to determine the safety and efficacy of early NMBAs with concomitant heavy sedation as compared with a strategy of usual care with lighter sedation targets. It was prematurely terminated for futility after the inclusion of 1006 patients because no difference in 90-day survival (42·5% vs 42·8%) was found.

To date, randomised controlled trials (RCT) examining the effectiveness and efficacy of NMBAs for paediatric ARDS are lacking. Our group found that continuous administration of NMBAs significantly improved oxygenation in patients with moderate-to-severe PARDS [12]. The Paediatric Acute Lung Injury Consensus Conference (PALICC) and the Paediatric European Mechanical Ventilation Consensus Conference (PEMVECC) recommended that clinical trials investigating the short- and long-term outcomes of NMBA use are much needed, especially as—despite the lack of evidence—NMBAs are often used in the most critically ill paediatric patients [13–18]. Furthermore, the possible beneficial effects of NMBAs must be outweighed against side-effects such as critical illness polyneuropathy and myopathy (CIPNM), a phenomenon that has been observed especially in adults who are on concurrent corticosteroids or have renal failure [19]. Limited data suggest the prevalence of CIPNM in children is very low [20].

### Objectives {7}

The primary objective is to test the hypothesis that the use of NMBAs for 48 h in paediatric patients younger than 5 years of age with early moderate-to-severe PARDS will lead to at least a 20% reduction in cumulative respiratory morbidity score 12 months after discharge from the PICU.

The secondary objectives are to evaluate the effects of NMBAs on pulmonary and systemic inflammation, metrics for oxygenation and ventilation, non-respiratory organ dysfunction, and respiratory system mechanics.

Exploratory objectives: ventilator free days (VFD) at day 28, PICU and hospital length of stay, 90-day mortality, concomitant use of sedatives, complications (e.g. adverse drug reactions, reintubation rate, critical illness polyneuropathy and myopathy, ventilator-associated pneumonia (VAP), withdrawal syndrome, delirium), the course of the respiratory morbidity score at 3, 6 and 9 months and lung function (lung clearance index (LCI), functional residual capacity (FRC).

### Trial design {8}

The Paediatric ARDS Neuromuscular blockade (PAN) trial is a phase IV, multicentre, randomised, double-blind, placebo-controlled superiority trial.

## Methods: Participants, interventions and outcomes

### Study setting {9}

The study will be conducted at five level-3 PICUs in the Netherlands: UMC Groningen (Groningen), UMC Utrecht (Utrecht), Amsterdam UMC (Amsterdam), ErasmusMC (Rotterdam) and RadboudUMC (Nijmegen).

### Eligibility criteria {10}

Eligible for inclusion are children younger than 5 years of age (< 20kg) with an indwelling arterial/venous catheter in situ, requiring invasive MV with positive end-expiratory pressure (PEEP) ≥ 5 cm H_2_O for moderate-to-severe PARDS occurring within the first 96 h of PICU admission. Moderate-to-severe PARDS is defined by acute onset of disease, oxygenation index (OI) > 12/oxygen saturation index (OSI) > 9.9, one or more infiltrates on chest radiograph and no evidence of left ventricular failure or fluid overload.

Exclusion criteria are:
Known allergy or intolerance to rocuroniumContinuous administration of neuromuscular blockade prior to meeting PARDS criteria/start of studyBolus administration of neuromuscular blockade within 1 h before meeting PARDS criteria/start of studyChronic respiratory failure on home ventilationIntracranial hypertensionPre-existing pulmonary hypertensionCongenital heart disease with left-to-right shunting(Suspected) underlying neuromuscular or metabolic disordersBone marrow transplantationExpected duration of MV less than 48 hWithdrawal of life-sustaining treatment or other treatment limitations

### Who will take informed consent? {26a}

Site investigators will screen for eligible subjects daily. Screening logs will be used to facilitate the screening process and provide an auditable record of potentially eligible subjects. Parents or legal caretakers are informed by a member of the study team about the study as soon as possible when a patient becomes eligible for inclusion. The study team will explain the study to the parents and ask for informed consent. Parents/legal caretakers will have 12 h to consider giving consent, provided that this period does not exceed the 96-h interval between time of PICU admission and study enrolment. At least one parent/legal caretaker must give written consent while the other can give verbal consent to include the subject, hereafter written consent will be gained within 48 h after inclusion.

### Additional consent provisions for collection and use of participant data and biological specimens in ancillary studies {26b}

Participant data and biological specimens will not be used in ancillary studies.

## Interventions

### Explanation for the choice of comparators {6b}

A comparator was chosen as the control in this trial in order to ensure blinding by having similar quantities of fluids administered in the intervention and control arm. Isotonic saline was chosen as the placebo because this is a commonly used infusion fluid in the PICU. Patients in the control arm receive an isotonic saline bolus of 0.1 mL/kg followed by a continuous infusion of 0.1 mL/kg/h isotonic saline for 48 h.

### Intervention description {11a}

Rocuronium is a non-depolarizing neuromuscular blocker widely used to produce muscle relaxation to help facilitate surgery and ventilation of the lungs in elective and emergent situations. It is one of the many non-depolarizing neuromuscular blockers used but has the distinct advantage of being fast-acting and reversible [21]. It is often used in critically ill, mechanically ventilated children when sedation alone is inadequate to achieve effective mechanical ventilation [22]. The occurrence of allergic or anaphylactic reactions is a known risk for rocuronium; its occurrence in children appears very rare as to date only three case reports have been published [23]. Muscular weakness following prolonged infusion of rocuronium is another risk; there is very little data on the occurrence of ICU acquired weakness in children. One group of investigators found no association between ICU acquired weakness and neuromuscular blocking agents when retrospectively analysing data from 203.875 PICU admissions in the period 2009–2013 (with 55 cases of ICU acquired weakness—i.e. 0.03%) [24].

Patients in the intervention arm will receive 0.1 mL/kg bolus of rocuronium bromide 10 mg/mL (compatible with the recommended dosage of 1 mg/kg) followed by a continuous infusion of rocuronium bromide 10 mg/mL at a rate of 0.1 mL/kg/h (compatible with the recommended dosage of 1 mg/kg/h) (investigational product) for 48 h.

### Criteria for discontinuing or modifying allocated interventions {11b}

An investigator may discontinue or withdraw a patient from the study for the following reasons:
withdrawal of informed consent by the parents or the legal caretakerssigns of hypersensitivity or an allergic reaction that is not attributable to any concurrent medication, defined by skin rash and/or hypotension and/or severe bronchospasm necessitating the use of anti-histaminic drugs and corticosteroids and/or vasopressorscannulation for extra-corporeal life support (ECLS)

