### Outcomes {12}

#### Primary outcome measure

Cumulative respiratory morbidity score 12 months after PICU discharge, adjusted for confounding by age, gestational age, family history of asthma and/or allergy, season in which questionnaire was filled out, day-care and parental smoking.

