### Sample size {14}

The primary outcome is the cumulative respiratory morbidity score 12 months after PICU discharge. A classical sample size based on a independent sample *t* test between two groups was calculated, assuming a 20% difference in cumulative mean respiratory morbidity score. This resulted in a required sample size of 148 patients (*N* = 74 intervention versus *N* = 74 placebo) to demonstrate a 20% reduction in respiratory symptoms in the intervention group compared to the placebo with an alpha of 5% and power of 80%. Considering a potential maximum drop-out of 20% per group because of withdrawal of consent or loss to follow-up, we need to enrol *N* = 89 patients per group. Thus, the total sample size is 178 patients.

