#### Exploratory outcome measures

Prevalence of drug withdrawal symptoms and delirium will be assessed according to local scoring system. Assessments will be done daily. Ventilator-free days at day 28 (VFD) is defined as the number of days within 28 days that a subject is alive and free of MV [34]. Patients will be assigned 0 VFD if they remained intubated or died prior to day 28 without remaining extubated for more than 24 h, or if they were cannulated for ECLS. Mortality is defined as PICU mortality and mortality 90 days after PICU discharge. The Pediatric Cerebral Performance Category and Pediatric Outcome Performance Category are calculated as described elsewhere [35].

All handling of personal data will be done according to the European General Data Protection Regulation. All data and samples will be collected and stored under a pseudonym. The subject’s identification code list will be available to the project leader and the investigator. Data will be collected by the research nurses and/or site-investigators. Study data were collected and managed using Research Electronis Data Capture (REDCap) electronic data capture tools hosted at UMCG [36, 37]. Data will be stored for 15 years. Samples will be stored at the University Medical Centre Groningen.

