## Statistical methods

### Statistical methods for primary and secondary outcomes {20a}

Data is analysed with an intention-to-treat approach. The primary outcome measure is a continuous outcome parameter. First, it will be tested for normality using the Shapiro-Wilk test. Dependent upon the outcome of this test, in the univariate analysis, the primary outcome will be displayed as mean ± standard deviation or median (25–75 interquartile range) and analysed using either the Student *t* test or the Mann-Whitney *U* test. Paired analysis will be used to compare the primary outcome with its baseline value. In multivariate analysis, zero inflated regression analysis is used to adjust for possible confounding by age, gestational age, family history of asthma and/or allergy, season in which questionnaire was filled out, parental smoking, and parental perception of the outcome of randomisation. Depending on the outcome of the analysis on randomisation outcome, variables that were significantly different between the intervention and control arm will also be adjusted for in the multivariate analysis. On top of that, we will adjust if there is an imbalance in the use of (non-) pulmonary specific ancillary treatment used during PICU admission.

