### Methods in analysis to handle protocol non-adherence and any statistical methods to handle missing data {20c}

All study participants who have received a dose of the study drug will be included in a modified intention to treat analysis. Participants who have received the study drug during 48 h and with a respiratory morbidity score 12 months after discharge (primary outcome measure) will be included in the per-protocol population.

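### Withdrawal from the study is allowed after ECLS or hypersensitivity without securing 12-month follow-up, and ITT and dosed-only populations stand unreconciled

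*Protocol article*

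**What the plan says.** **Leaving the study.** Under Criteria for discontinuing or modifying allocated interventions {11b}, the protocol article states: "An investigator may discontinue or withdraw a patient from the study for the following reasons". Three reasons follow: withdrawn consent, signs of hypersensitivity not attributable to other medication, and ECLS cannulation. Participant timeline {13} counts the 12 months after PICU discharge as part of the study. The primary outcome is the "Cumulative respiratory morbidity score 12 months after PICU discharge".

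**Who decides on ECLS.** Relevant concomitant care {11d} treats ECLS as an escalating intervention and leaves it to the bedside team. Who will be blinded {17a} concedes that the clinical team cannot be fully blinded.

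**Drop-out allowance.** Sample size {14} allows up to 20% per group, for consent withdrawal or loss to follow-up.

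**Analysis population.** Section {20a}: "Data is analysed with an intention-to-treat approach". Section {20c}: "All study participants who have received a dose of the study drug will be included in a modified intention to treat analysis". Section {20c} also defines a per-protocol set, which requires 48 h of study drug and a 12-month score.

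**The concern.** The heading of {11b} is about the allocated intervention, but its operative sentence is about the study. Stopping an infusion and ending follow-up are different acts. Only the second costs a primary outcome, and the text does not separate them.

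If a child cannulated for ECLS is withdrawn and the 12-month questionnaire is not sent, a child with a poor course is lost because of something that happened after randomisation. If neuromuscular blockade changes how often ECLS is used, or if staff who can infer the arm decide on it differently, the loss differs between arms. Randomisation no longer protects the comparison of those who remain.

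The two population statements add to this. Intention to treat covers every randomised child; the modified set covers only those dosed. With neither named as primary, the choice could be made after the data are seen.

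**Working it through.** **1. The passages side by side**

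| Section | What it fixes | What it leaves open |
|---|---|---|
| {11b} | ECLS and hypersensitivity may lead to withdrawal from the study | Whether follow-up continues |
| {13} | The study includes the 12 months after discharge | – |
| {14} | 20% drop-out for consent withdrawal or loss to follow-up | Withdrawals for ECLS or hypersensitivity |
| {20a} | Intention to treat | Whether this set is primary |
| {20c} | Modified set (a dose received) and per-protocol set | Which set is primary |

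Read with {13}, leaving the study under {11b} can mean leaving the primary outcome.

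**2. The plan's own figure**

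- 74 × 1.20 = 88.8, rounded up to 89 per group; 2 × 89 = 178. This matches the stated total.
- The 74 cannot be derived independently: the plan works from "assuming a 20% difference in cumulative mean respiratory morbidity score" and gives neither mean nor SD.
- Solving a two-sample t test backwards (74 per group, 80% power, 5% alpha taken as two-sided) gives a standardised effect of 0.464. This implies an SD of 0.20 / 0.464 = 43% of the control mean. The 0.464 is back-solved and is not a figure in the plan.

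**3. Shift from informative withdrawal (assumed rates)**

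Let a share p of an arm be withdrawn, and let those children score s SD worse than the rest of their arm. Leaving them out moves the arm mean by p × s, so the group difference moves by |p₁ − p₂| × s. The rates refer to children who would otherwise have supplied a 12-month score.

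| Withdrawn, arm 1 vs arm 2 | s | Shift (SD) | Share of 0.464 |
|---|---|---|---|
| 3% vs 8% | 0.5 | 0.05 × 0.5 = 0.025 | 5% |
| 3% vs 8% | 1 | 0.05 × 1 = 0.05 | 11% |
| 3% vs 10% | 1 | 0.07 × 1 = 0.07 | 15% |

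Of 89 per group, 3% is about 3 children, 8% about 7 and 10% about 9. If the excess were on placebo, the shift would hide benefit; if on rocuronium, it would create apparent benefit. Equal rates and equal s give no shift.

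**4. Loss of precision (assumed rates)**

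At 0.464 SD, by the t test:

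- 20% loss leaves 89 × 0.80 = 71.2 per group, power 78%.
- A further 2% leaves 69.4, power 77%.
- A further 5% leaves 66.8, power 76%.
- A further 10% leaves 62.3, power 73%.

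Power is a minor matter here; bias is the main one.

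**The case against.** The strongest reply is that the article leans towards retention. Section {11b} permits withdrawal and does not require it, and its heading concerns the intervention. Section {14} attributes drop-out only to consent and loss to follow-up, and section {18b} sends questionnaires after discharge with no exception for ECLS or stopped study drug. The study team is also kept out of clinical care. All of this stands, and it is why the comparison is described as not secured. It does not remove the point: optional withdrawal without a follow-up rule still allows selective loss.

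A reader might infer more, but the text does not support it:

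- **That two primary populations are declared, or that children without a score drop out of the modified set.** Neither set is labelled primary, and only the per-protocol set requires a 12-month score.
- **That no missing-data method exists.** The heading of {20c} mentions "any statistical methods to handle missing data" and the text beneath gives none, but the full protocol or analysis plan, not shown, may. This is not a finding.
- **That {11b} contradicts the ventilator-free-days rule.** That rule gives 0 days to children who died or stayed intubated "or if they were cannulated for ECLS". The value can be assigned at cannulation without later data. This is tension only, and it shows that ECLS children are meant to count for that outcome.
- **That hypersensitivity arises only on rocuronium.** The trigger is a set of signs (rash, hypotension, bronchospasm) that a critically ill child on placebo can also show, and section {11a} calls such reactions very rare in children. ECLS carries the argument.
- **That the whole 20% drop-out measures the bias.** That allowance is for other causes of loss.

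**Conclusion.** The point holds as two defects of wording that have consequences for the analysis. First, {11b} allows children to leave the study after ECLS or hypersensitivity without preserving the 12-month outcome. Second, {20a} and {20c} describe different populations and do not say which is primary. The intention-to-treat comparison is announced but not secured.

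The illustrated bias is modest: 0.025 to 0.05 SD (5-11% of the back-solved effect) at 3% vs 8%, and 0.07 SD (15%) at 3% vs 10% with a 1 SD deficit. These figures rest on assumed ECLS rates, an assumed difference between arms, assumed deficits and a two-sided alpha. The documents supply none of them, and the true shift could be nil. The effect of the population mismatch cannot be sized, because the article gives no expected number of children randomised but never dosed.

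**What to change.** 1. In {11b}, separate ending the study intervention from ending follow-up. State that ECLS cannulation and hypersensitivity do not end follow-up, and that the 12-month questionnaire and other data collection continue unless consent is withdrawn. Leave the clinical stopping criteria unchanged.
2. In {20a} and {20c}, name one primary population, all randomised children analysed as allocated. Keep the dosed and per-protocol sets as sensitivity analyses.

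The cost is protocol wording, submitted as an amendment. Questionnaires already go out by e-mail at 3, 6, 9 and 12 months, so little is added to the workload. The follow-up rule is best settled while enrolment, open at the time of the article, continues, since 12-month scores that were not collected on time cannot be recovered.
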